### 2.5. Ethics

Permission to conduct the study and to collect the data has already been obtained from the Ethical Committee of the University Hospital Bratislava–Hospital of Ladislav Dérer, the Academician (number 31/2020), following the ethical standards of the Helsinki Declaration and its later amendments. The data collection procedure is explained to all participants before data collection on their voluntary participation and the right to withdraw from the study without any consequences. The study is registered under the Clinical trials gov., registration number: NCT05053282. The full protocol and dataset are available from the corresponding author on reasonable request.

### 2.6. Study Procedures

#### Familiarization

A familiarization session will be held on Monday, 2 days before performance testing, to secure the physical performance tests’ validity. Firstly, subjects will bring signed informed contents and fill in the questionnaires. Afterward, each participant will undergo a medical check consisting of heart rate, blood pressure, resting ECG measurements, and anamnesis realized by a medical doctor. After the medical check, subjects will be familiarized with each testing procedures and equipment.

## 3. The Primary Outcome

The primary outcome measurements will be represented by the VO_2peak_ reached in the cardiorespiratory fitness testing on the cycle ergometer, as these parameters define the physical fitness level for each subject.

### Cardiorespiratory Fitness

Cardiorespiratory fitness will be measured by the direct measurement of the VO_2peak_ through a graded cycling ergometry in a room with a standard temperature and humidity. Due to safety considerations, we decided to use cycling ergometry instead of treadmill walking/running considering the limitations of this procedure [28].

Protocols for cycle ergometry testing will include an initial 3-min warm-up period with a load between 20 and 100 Watts (W) followed by maximal graded exercise with an incremental load between 20 and 30 W/min. The load will be set individually for each subject depending on the predicted work capacity according to the reference values and the participant’s estimated fitness level [8].

The cardiorespiratory variables, VO_2_, carbon dioxide production, respiratory exchange ratio, and pulmonary ventilation will be measured using a gas analyzer Power Cube (Ganshorn Medizin Electronic, Niederlauer, GER) coupled to the computerized system, with samples every 10 s. The gas analyzer of O_2_ and the room environment will be calibrated according to manufacturer’s specification before each test.

The VO_2peak_ will be considered as the highest value obtained during the test. The blood pressure will be monitored before, throughout, and after the test by Metronik BL-6 (STOLL Medizintechnik, Waiblingen, GER), and the heart rate (HR) by 12-lead ECG Quark T12 (Cosmed, Rome, ITA, Rome, Italy). The test will be carried out by an exercise physiologist and a medical doctor.

## 4. Secondary Outcome Measure

### 4.1. Questionnaires

At the familiarization session, subjects will obtain the following questionnaires: (1) Quality of Life Questionnaire (DABQ), (2) Low Energy Availability in Females Questionnaire (LEAF-Q) [29], and (3) The Aging Males Symptoms Scale (AMS) [30]. Currently, there is no similar questionnaire for male athletes as LEAF-Q. Therefore, we decided to use them without questions according to menstruation. The LEAF-Q, along with AMS, will be used to examine the prevalence of RED-S. The questionnaires will be evaluated separately. The questionnaires were translated into the Slovak language according to the WHO [5].

### 4.2. Body Composition and Bone Status

The basic anthropometric parameter measurements such as body height and body weight are the input parameters for measuring body composition by the DXA. Body height will be measured and determined to the nearest centimeter on a digital free-standing stadiometer InBody BSM 170 (InBody Co., Ltd., Cerritos, CA, USA). Body weight will be set, with subjects wearing underwear on Body 230 (InBody CO., Ltd., Cerritos, CA, USA). Afterward, the BMI will be calculated.

The bone mineral density, content, and total and regional body composition will be assessed from a total body DXA scan. The testing procedure of DXA will be realized according to Kralik et al., 2019 [31]. The subjects will be positioned in a supine position in the middle of the densitometry table with their head straight, space between their arms and torso, palms flat on the table, and feet together secured by a strap. A certified radiologist will conduct all DXA procedures.

### 4.3. Muscular Strength

Lower body strength will be measured as a maximal voluntary contraction (MVC) and rate of torque development (RTD) of both isometric extension and flexion on knee dynamometer (ARS dynamometry, S2P Ltd., Ljubljana, Slovenia) [32,33]. For both tests, subjects will perform two warm-up trials with approximately 50% and 80% of maximal effort with a 30-s rest interval [20,31]. Subsequently, three trials will be performed with maximal effort and will be recorded. The subjects will be instructed to push/pull as fast and hard as possible and hold for 5 s against the lever arms [34,35]. The resting interval will be 90 s between the trials and 3 min between the extension and flexion measurement. Monitored parameters will be the peak torque and RTD in four intervals: 0–50, 0–100, 0–150, and 0–200 ms, respectively. Attempts with the highest values will be used for further analyses.

Upper-body strength will be assessed through the isometric MVC handgrip test by Camry Digital Hand Dynamometer (Zhongshan Camry Electronic, Zhongshan, China). Each subject will be in a seated position with the shoulder adducted, the elbow flexed at 90 degrees, and the wrist flexed between 0 and 30 degrees [36]. The subject will perform three trials for each hand with maximal effort. A one-minute rest interval will be between trials and hands. Attempts with the highest values for each hand will be used for further analyses.

### 4.4. The Physical Activity Monitoring Period

The subjects’ daily physical activity will be tracked using an accelerometer AactivPAL4 (PAL Technologies Ltd., Glasgow, Scotland) that is designed to quantify free-living daily activities. ActivPAL uses information about static and dynamic acceleration to (1) distinguish body posture as sitting/lying, standing, and stepping, and (2) estimate energy expenditure expressed as metabolic equivalents—METs [37]. The accelerometer will be worn under clothing on the anterior midline of the right thigh (half the distance between the knee and the hip). After the physical fitness testing session, the researcher will attach the activPAL to the participants’ thigh using flexible waterproof sleeves and waterproof medical grade adhesive dressing (TegadermTM, 3M Co., St. Paul, MN, USA). Subjects will be requested to continuously wear the accelerometer 24 h per day for 12 days [38]. The subjects will be asked to avoid swimming, sauna, or staying in other wet environments. They will only be allowed to shower. If accelerometers were to be removed for legitimate reasons, the subjects will be required to record in the diary all non-wear periods (such as period/reason), as well as times of getting up, falling asleep, or taking naps. Subjects will be requested to wear the ActivPAL for 12 days and perform their daily activities as usual. However, only 7 days (from Monday to Sunday) will be used for further analyses (Figure 1). Additionally, the participants from athletic groups will be requested to have standard light running training on the last day of the tracking period, as long as it is 24 h before muscle biopsy sampling.

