### 4.5. Dietary Tracking

Diet records will be tracked within the seven days (Monday to Sunday) while the subjects will be wearing the accelerometers. Subjects will be educated on dietary reporting strategies, such as servings sizes and comparisons of everyday household items. Energy (kilocalorie) and macronutrients (carbohydrate, fat, and protein) data will be retrieved from each participant’s diary and expressed as a daily average for total and relative intakes. Additionally, a timeline of energy and macronutrient intake during the whole day will be created to identify individual differences and deficiencies (frequency of eating, habits, continuity of food, and training). All analyses will be conducted by nutritional software PLANEAT (Planeat Ltd., Bratislava, Slovakia), which has been previously described by Bajer et al. (2019) [39]. A single researcher will analyze the dietary data to avoid variability in the interpretation of these data.

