### 4.6. Blood Collection and Analyses

The venous blood collection will be held 13 days after the physical performance testing session (Figure 1) and collected by a nurse at the hospital. The participants will arrive at the hospital by car between 7:30 a.m. and 8 a.m. The subjects will also be instructed to come after overnight fasting. Blood samples will be collected in several tubes. Plasma will be obtained from venous blood collected into K3EDTA tubes and then centrifuged at 4 °C for 10 min at 1000× *g*. After centrifugation, blood plasma will be collected and stored at −80 °C until processing via an enzyme-linked immunosorbent assay (ELISA) to analyze inflammatory markers (IL-1β, IL-6, TNF-α, CRP), malnutrition biomarkers (transthyretin and retinol binding protein), as well as metabolic hormones (e.g., leptin, adiponectin, ghrelin, and thyroid hormones) held by our laboratory.

Additionally, basic biochemical parameters and malnutrition biomarkers, including glucose, urea, creatinine, uric acid, total proteins, albumins, transthyretin, and retinol binding protein, total bilirubin, alkaline phosphatase, aspartate aminotransferase, alanine aminotransferase, γ-glutamyltransferase, total cholesterol, low-density lipoprotein cholesterol, high-density lipoprotein cholesterol, triacylglycerols, and glycated hemoglobin HbA1c, will be analyzed in blood samples by a commercial medical laboratory.

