### 4.7. Muscle Sampling and Analyses

The muscle biopsy will be held after the blood collection (Figure 1). The procedure will be performed at the hospital by a medical doctor and nurse. Subjects will be instructed to avoid any strenuous physical activity 48 h before the procedure and come in the fasted state. The biopsy will be performed with the subject in a supine position and under local anesthesia (lidocaine 2%) using a percutaneous muscle biopsy technique using the sterile Bergström needle (Bergström-Stille, Sweden, 5 mm) with manual suction to obtain muscle specimens (approximately 80 mg) from the mid-section of the right m. vastus lateralis [31]. Afterwards, visible connective tissue and fat will be dissected away from samples.

For histology and immunohistochemistry, a bundle of fibers will be mounted in cryomolds with an OCT embedding compound and snap-frozen immediately in liquid nitrogen-cooled isopentane. The samples will be stored at −80 °C for further analyses. Afterwards, the samples will be cut at an 8 μm thickness at −21 °C using a cryostat and mounted on microscope slides. The sections will be stained and analyzed for their muscle fiber morphometry, nuclear number and myonuclear domain, satellite cells, and capillaries.

The muscle samples for the molecular analyses will be snap-frozen only in liquid nitrogen and stored at −80 °C for further analyses. The tissue will be used for gene expression analysis (PCR). Target genes will include inflammatory markers (e.g., IL-1β, IL-6, TNFα, COX-2) and markers of muscle differentiation and atrophy (e.g., Atrogin-1, MuRF-1, FoxO, MyoD).

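### If the biopsy follows the blood draw at the same visit, the analysed Monday-to-Sunday week ends on a Sunday partly under the 48 h limit on strenuous activity, which can modestly understate the runners' usual activity

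*Protocol article*

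**What the plan says.** All of the following is in the protocol article.

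- Section 2.6 (Familiarization) fixes the weekday: "A familiarization session will be held on Monday, 2 days before performance testing".
- Section 4.4 starts the wear period: "After the physical fitness testing session, the researcher will attach the activPAL to the participants’ thigh". Its length is 12 days, and the instruction is to live normally: "Subjects will be requested to wear the ActivPAL for 12 days and perform their daily activities as usual". The analysis uses less than what is recorded: "However, only 7 days (from Monday to Sunday) will be used for further analyses (Figure 1".
- Section 4.4 also asks the athletes for a light run on the last tracking day, provided that this is 24 h before the biopsy.
- Section 4.5 ties the diet record to that week: "Diet records will be tracked within the seven days (Monday to Sunday").
- Section 4.6 dates the blood draw: "The venous blood collection will be held 13 days after the physical performance testing session". Arrival is between 7:30 and 8 a.m., fasted.
- Section 4.7 places the biopsy after the blood collection, also fasted, and adds: "Subjects will be instructed to avoid any strenuous physical activity 48 h before the procedure".

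Nothing in the article excludes or adjusts for restricted time in the activity or diet averages.

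**The concern.** Section 4.4 treats the analysed week as free-living activity, while section 4.7 limits what subjects may do in the two days before the biopsy. If the two periods overlap, part of the analysed week is not usual activity.

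The instruction covers everyone, but it changes behaviour mainly in men who run more than 300 min per week. Men selected for no regular training have little strenuous activity to give up. Any error therefore differs between groups and pulls the athlete and sedentary means for activity closer together. Activity level is also an explanatory factor in the study objectives, and section 4.8 compares the groups on every measured parameter. Diet on the affected day could shift as well.

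**Working it through.** **Inputs.** Familiarization on Monday, testing 2 days later (section 2.6). ActivPAL attached after testing and worn for 12 days (4.4). Blood 13 days after testing, arrival 7:30 to 8 a.m. (4.6). Biopsy after blood, with 48 h without strenuous activity beforehand (4.7). Athletes run more than 300 min per week (2.4).

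**Step 1: the calendar.** Monday + 2 days = Wednesday, taken as day 0. Day 4 is then Sunday, day 5 Monday, day 10 Saturday, day 11 Sunday, day 12 Monday and day 13 Tuesday.

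**Step 2: the analysed week.** Wear runs from day 0 to day 11 or day 12, depending on whether the testing day counts as the first of the 12. Either way it holds exactly one full Monday-to-Sunday block, days 5 to 11.

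**Step 3: the biopsy day.** The article does not state it, and Figure 1 is not shown. Section 2.2 gives 3 visits in total. Familiarization and testing take two, which leaves one for blood and biopsy, and both of these are taken fasted. The same-visit reading puts the biopsy on Tuesday, day 13. It also fits the light-run clause: if day 12 (Monday) is the last tracking day, a run 24 h before the biopsy falls there.

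**Step 4: the overlap.** Start of restriction = biopsy time − 48 h.

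- Tuesday 08:00 − 48 h = Sunday (day 11) 08:00, so 24 − 8 = 16 h of that Sunday are restricted.
- Biopsy at 10:00, 12:00 or 15:00: 14 h, 12 h or 9 h of Sunday.
- If the 13 days are counted inclusively, the biopsy is on Monday, day 12. All of Sunday is restricted, and so is Saturday (day 10) from 08:00.
- If the biopsy is one day after the blood draw (Wednesday), the restriction opens on Monday and no hour of Sunday is affected.

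**Step 5: size on the Tuesday reading.** Under-reading of weekly running = Sunday's share of the week × fraction of Sunday's running lost. At the entry minimum of 300 min, spread evenly, Sunday's share is 1/7, or 300/7 = 43 min. The fractions lost are assumptions:

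- 25% lost: 1/7 × 0.25 = 3.6%, about 11 min
- 50% lost: 1/7 × 0.50 = 7.1%, about 21 min
- 100% lost: 1/7 × 1.00 = 14.3%, about 43 min

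**Step 6: is a clear week available?** On the Tuesday reading, days 1 to 10 are complete worn days before the restriction. Days 4 to 10 (Sunday to Saturday) hold each weekday once, begin four days after the maximal test and end 8 h before Sunday 08:00. They share days 5 to 10, six of seven, with the present week. On the Monday reading only days 1 to 9 are clear, and days 3 to 9 would serve.

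**The case against.** The strongest reply is that the biopsy day is nowhere stated. Section 4.7 gives only the order, and the site descriptions do not help: section 2.2 places blood collection at the faculty centre, section 4.6 at the hospital. A biopsy a day or more after the blood draw would remove the overlap. This stands as a condition on the whole point, although the three visits and the shared fasting make the same visit the natural reading.

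A reader might also infer that the athletes' Sunday is a lost training day. The documents do not support that. Only strenuous activity is barred, and section 4.4 itself asks for a light run inside the 48 h before the biopsy. If tracking ends on Sunday, that light run is requested on the analysed day itself. A run finished before about 8 a.m. also precedes the restriction. A figure of 30% would need a 90-min Sunday run (90/300) given up entirely; both the run and its full loss are assumptions.

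A reader might further infer that energy balance would look too favourable in the athletes. No stated analysis sets activPAL expenditure against intake: section 4.1 examines relative energy deficiency by questionnaire, and section 4.5 reports intake as daily averages. Nor does the overlap affect who is in which group, since section 2.4 defines the groups by training history.

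**Conclusion.** The point holds, conditional on a same-visit biopsy. On the stated days, the last of the seven analysed days is then partly under a limit on strenuous activity, in a week meant to show usual activity.

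The likely effect is a modest understatement of the runners' activity and some shrinkage of the athlete-sedentary contrast. The bound on the Tuesday reading is about one day's running, 14% of the week if evenly spread, and the true figure is probably lower. A Monday biopsy would extend the restriction to most of Saturday as well.

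Only secondary measures are touched. VO2peak, the primary outcome, is measured before the accelerometer is attached. It would be too much to say that the calendar is fully fixed by the text, or that seven unrestricted days exist for both measures: that is true of the accelerometer but not of the diet record, which covers the Monday-to-Sunday week alone.

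**What to change.** - State the day of the biopsy relative to testing, and reconcile sections 4.4, 4.5 and 4.7 on usual activity, the analysed week and the pre-biopsy restriction. The restriction itself need not change for this purpose.
- For men still to be measured, analyse Sunday to Saturday (days 4 to 10) and start the diet diary on that same Sunday.
- For men already measured, derive the activPAL week as days 4 to 10 from the 12 recorded days, so that one window applies to everyone. Report that their diet record overlaps it on six of seven days.
- If the biopsy proves to be on Monday, use an earlier seven-day window that ends before the restriction, for example days 3 to 9, and move the diary to match. If it falls a day or more after the blood draw, the present week can stay.

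The cost is a one-day shift of the analysis window and diary, with no extra wear or visits. The downside is the one-day mismatch between activity and diet in men already measured, whose diet record cannot be moved.

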### 4.5. Dietary Tracking

Diet records will be tracked within the seven days (Monday to Sunday) while the subjects will be wearing the accelerometers. Subjects will be educated on dietary reporting strategies, such as servings sizes and comparisons of everyday household items. Energy (kilocalorie) and macronutrients (carbohydrate, fat, and protein) data will be retrieved from each participant’s diary and expressed as a daily average for total and relative intakes. Additionally, a timeline of energy and macronutrient intake during the whole day will be created to identify individual differences and deficiencies (frequency of eating, habits, continuity of food, and training). All analyses will be conducted by nutritional software PLANEAT (Planeat Ltd., Bratislava, Slovakia), which has been previously described by Bajer et al. (2019) [39]. A single researcher will analyze the dietary data to avoid variability in the interpretation of these data.

### 4.6. Blood Collection and Analyses

The venous blood collection will be held 13 days after the physical performance testing session (Figure 1) and collected by a nurse at the hospital. The participants will arrive at the hospital by car between 7:30 a.m. and 8 a.m. The subjects will also be instructed to come after overnight fasting. Blood samples will be collected in several tubes. Plasma will be obtained from venous blood collected into K3EDTA tubes and then centrifuged at 4 °C for 10 min at 1000× *g*. After centrifugation, blood plasma will be collected and stored at −80 °C until processing via an enzyme-linked immunosorbent assay (ELISA) to analyze inflammatory markers (IL-1β, IL-6, TNF-α, CRP), malnutrition biomarkers (transthyretin and retinol binding protein), as well as metabolic hormones (e.g., leptin, adiponectin, ghrelin, and thyroid hormones) held by our laboratory.

Additionally, basic biochemical parameters and malnutrition biomarkers, including glucose, urea, creatinine, uric acid, total proteins, albumins, transthyretin, and retinol binding protein, total bilirubin, alkaline phosphatase, aspartate aminotransferase, alanine aminotransferase, γ-glutamyltransferase, total cholesterol, low-density lipoprotein cholesterol, high-density lipoprotein cholesterol, triacylglycerols, and glycated hemoglobin HbA1c, will be analyzed in blood samples by a commercial medical laboratory.

### 4.7. Muscle Sampling and Analyses

The muscle biopsy will be held after the blood collection (Figure 1). The procedure will be performed at the hospital by a medical doctor and nurse. Subjects will be instructed to avoid any strenuous physical activity 48 h before the procedure and come in the fasted state. The biopsy will be performed with the subject in a supine position and under local anesthesia (lidocaine 2%) using a percutaneous muscle biopsy technique using the sterile Bergström needle (Bergström-Stille, Sweden, 5 mm) with manual suction to obtain muscle specimens (approximately 80 mg) from the mid-section of the right m. vastus lateralis [31]. Afterwards, visible connective tissue and fat will be dissected away from samples.

For histology and immunohistochemistry, a bundle of fibers will be mounted in cryomolds with an OCT embedding compound and snap-frozen immediately in liquid nitrogen-cooled isopentane. The samples will be stored at −80 °C for further analyses. Afterwards, the samples will be cut at an 8 μm thickness at −21 °C using a cryostat and mounted on microscope slides. The sections will be stained and analyzed for their muscle fiber morphometry, nuclear number and myonuclear domain, satellite cells, and capillaries.

The muscle samples for the molecular analyses will be snap-frozen only in liquid nitrogen and stored at −80 °C for further analyses. The tissue will be used for gene expression analysis (PCR). Target genes will include inflammatory markers (e.g., IL-1β, IL-6, TNFα, COX-2) and markers of muscle differentiation and atrophy (e.g., Atrogin-1, MuRF-1, FoxO, MyoD).

For transmission electron microscopy (EM), the muscle sample of each subject will be fixed in freshly prepared 3.5% glutaraldehyde in 0.1 M cacodylate (NaCaCO) buffer, pH 7.4. The fixed bundles of fibers will be stored at 4 °C, until embedding. Afterwards, quantitative analyses of calcium release units (CRUs or triads), mitochondria, and calcium release units (CEUs) will be performed. The following parameters will be quantified: (1) number of CRUs/area, (2) number of mitochondria and mitochondria-CRUs pairs/area [40,41], and (4) CEUs which are formed by SR-stacks (a) and elongated T-tubules at the I band (b). They will be quantified as follows: (a.) percentage of fibers presenting SR-stacks and number of SR-stacks/(per) 100 μm^2^, (b.) we will determine both: (i) the extension of the SR in close association with the T-tubule in 100 μm^2^ of section, and (ii) the total extension of the T-tubule network in 100 μm^2^ of section.

